### **3.2 Randomization.**

Stratified and block randomization methods are employed. SAS statistical software is used to generate the 'Center Code Randomization Table' based on the number of cases from participating units and the randomization ratio. The selected block length, randomization seed parameters, and other confidential data were sealed in the blind envelope. Unrelated personnel encoded the drugs according to this randomization table. The intervention group and control group are allocated in a 1:1 ratio.

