### **3.4 Sample size calculation**

The sample size is calculated based on the estimated post-treatment CT-FFR values. The PROMISE study revealed an average CT-FFR value of  $0.77 \pm 0.1$  for patients with ICL. A clinical study indicated that after traditional Chinese medicine intervention, patients with CAD had CT-FFR values of  $0.92 \pm 0.16$ . Therefore, it was assumed that the CT-FFR value in the control group is 0.77 and the value in the intervention group could be elevated to 0.92 after treatment, the standard deviation  $\sigma = 0.13$  for both two groups. Results from the NXT study indicated that for every 0.05 unit decrease in CT-FFR, there was an independent correlation with the increasing rate of composite cardiovascular events. Based on this, we have set the cut-off value  $\Delta=0.03$  in this superiority trial. The number of cases in the two groups is arranged in a ratio of 1:1, so  $c=1$ . Given a type I error rate of  $\alpha = 0.05$  (two-side test), a power of 95% (type II error rate of  $\beta = 0.05$ ), so  $u_\alpha=1.96$ ,  $u_\beta=1.64$ ,  $n_1=n_2\approx 55$ . Considering the maximum dropout rate of 10%, a total of 120 patients is needed. The calculation formula is as follows:

$$n_1 = \left(\frac{1+c}{c}\right) \left[\frac{(u_\alpha + u_\beta) \sigma}{\mu_T - \mu_C - \Delta}\right]^2 + \frac{1}{4} u_\alpha^2, \text{ and } n_2 = c n_1$$

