## **9. Statistical Analysis**

All statistical tests will be conducted as two-tailed tests, and a P-value  $\leq 0.05$  will be considered statistically significant for the tested differences.

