  - Estimation: The least squares method will be used to estimate the mean difference between groups and the 95% CI.
- c) Serum inflammatory factors, blood lipids, and carotid ultrasound indicators
- Description: Values at baseline and 6 months after treatment, as well as the difference from baseline to 6-month will be described.
  - Intergroup Comparisons: A linear mixed model will be used, with the dependent variable being the difference from baseline to 6-month. Fixed effects include group and center, and random effects include the subjects, with baseline values as covariates.

- Estimation: The least squares method will be used to estimate the mean difference and 95% CI.
- 3) Endpoint Event: MACE
- Description: The incidence rate of MACE from baseline to the 1-year follow-up will be described.
  - Intergroup Comparisons: The Cox proportional hazards model will be used, with the dependent variable being the occurrence of MACE and the survival time variable being the time from baseline to either the occurrence of MACE or the end of follow-up. The primary independent variable is the group. Covariates include age, gender, BMI, systolic blood pressure, diastolic blood pressure, LDL-C, FBG, smoking status, alcohol consumption, family history of early-onset cardiovascular disease, presence of cerebrovascular disease, peripheral vascular disease, diabetes mellitus, hypertension, dyslipidemia, concomitant use of PCSK-9 inhibitors, and study center.
  - Estimation: The partial likelihood method will be used to estimate the hazard ratio and its 95% CI.
- 4) Subgroup analyses: Considering the significant impact of concomitant diabetes and the use of PCSK-9 inhibitors on drug efficacy, subgroup analysis of the primary efficacy outcome and endpoint events will be performed in SCAD patients with diabetes and SCAD patients with the use of PCSK-9.

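### The MACE Cox model has at least 19 coefficients in a 120-patient trial: its treatment hazard ratio is unreliable at 12–24 events and often not finite at about 6

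*Protocol*

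**What the plan says.** Protocol section 9.2.2, item 3, fixes the between-group analysis of MACE: "The Cox proportional hazards model will be used, with the dependent variable being the occurrence of MACE". Time runs from baseline to the event or the end of follow-up, and group is the main independent variable. The listed adjustments are:

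- six continuous variables: age, BMI, systolic and diastolic pressure, LDL-C and fasting glucose;
- ten characteristics that can be coded as binary: sex, smoking, alcohol, family history, cerebrovascular disease, peripheral vascular disease, diabetes, hypertension, dyslipidemia and PCSK-9 inhibitor use;
- study center.

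The hazard ratio and its interval are to come from the partial likelihood. No variable selection, penalisation, minimum event count or fallback is given.

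Section 3.1 names three centers. Section 3.4 sizes the trial on CT-FFR and concludes that "a total of 120 patients is needed". No MACE rate, event count or power is stated anywhere. Section 5.4 lists MACE on its own, outside the primary (5.2.1) and secondary (5.2.2) efficacy outcomes. Item 4 of section 9.2.2 adds that "subgroup analysis of the primary efficacy outcome and endpoint events will be performed" in patients with diabetes and in users of PCSK-9 inhibitors, without naming a model.

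**The concern.** A Cox model draws its information from events, not from patients. A model with more coefficients than events tends to overfit. Some coefficients run off to infinity, standard errors are too small for the real variability, and the treatment estimate drifts away from 1.

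MACE is the only clinical-event efficacy endpoint in the trial, so a striking hazard ratio would attract attention whatever its formal rank. If the model fails at analysis, the covariates to drop would have to be chosen after the data are seen, which defeats the purpose of naming them in advance. Because the protocol fixes both the covariates and the estimator, this is a choice made badly and not a detail left for a statistical analysis plan.

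**Working it through.** **Stated figures.** There is no MACE calculation to reproduce. The only sizing figure is about 55 per arm for CT-FFR. The protocol's formula with its own inputs gives 2 × [(1.96 + 1.64) × 0.13 / (0.92 − 0.77 − 0.03)]² + 1.96²/4 = 30.42 + 0.96 = 31.4, so the 55 does not reproduce. That is a separate matter. The check below takes the planned 120 as given.

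**Coefficient count.** Group 1 + covariates 16 + center (3 − 1) = 19. This is a minimum, because smoking or alcohol with more than two levels would add terms.

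**Events per coefficient.**
- Ten per coefficient: 19 × 10 = 190 events, more than 120 patients.
- Five per coefficient: 19 × 5 = 95 events, and 95/120 = 79% of patients.
- If every patient had an event: 120/19 = 6.3 per coefficient.

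This mismatch needs no assumed event rate.

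**Simulation.** Fixed inputs: 120 patients, allocation 1:1, three centers, two-sided 5% test. Assumed inputs: MACE rates of 5–20%, covariate prevalences, and modest covariate effects. There were 400 trials per event count, with a true treatment hazard ratio of 1. Events = 120 × rate. The group estimate counted as not finite if the fit was perfect, the absolute log hazard ratio exceeded 8, or its standard error exceeded 10 or was not finite. U/L is the median ratio of upper to lower 95% limit. The false-positive, U/L and extreme-estimate columns for the full model are among finite estimates.

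| Assumed rate | Events | Events per coefficient | Full model: group HR not finite | False positives | U/L | HR above 3 or below 1/3 | Group-only: false positives | Group-only: U/L |
|---|---|---|---|---|---|---|---|---|
| 5% | 6 | 0.32 | 54.5% | 0% | 428 | 50.5% | 0% | 29.8 |
| 10% | 12 | 0.63 | 0.25% | 10.5% | 23.8 | 27.8% | 3.25% | 9.9 |
| 15% | 18 | 0.95 | 0% | 11% | 10.2 | 15.2% | 6.5% | 6.4 |
| 20% | 24 | 1.26 | 0% | 6.8% | 6.9 | 5.2% | 2.75% | 5.0 |

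With 400 runs, the standard error of a 10.5% rate is about √(0.105 × 0.895/399) = 1.5 percentage points. The excess over 5% is clear at 12 and 18 events. At 24 events this run alone does not establish it.

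A separate null simulation, also 400 runs per event count with assumed prevalences, agreed. The group estimate was finite in 56% of runs at 6 events (U/L about 250). At 12, 18 and 24 events the false-positive rates were 9%, 8% and 7%, with U/L of 20, 10 and 6.6. The group-only model stayed at 0–5%.

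**Exaggeration.** With a true hazard ratio of 0.5 (500 runs per event count), the median estimate among fits in which every coefficient converged was 0.38, 0.41 and 0.42 at 12, 18 and 24 events.

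**Beyond the range.** At 36 events (a 30% rate), interval coverage was still about 90–92%, not 95%.

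**Limits of the simpler model.** By Schoenfeld's approximation, power for a hazard ratio of 0.5 at 12 events is Φ(√(12/4) × ln 2 − 1.96) = Φ(1.20 − 1.96) = Φ(−0.76) ≈ 22%. The expected U/L is exp(2 × 1.96 × 2/√12) ≈ 9.6, close to the simulated 9.9.

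**The case against.** The strongest reply is that MACE is neither a primary nor a listed secondary efficacy outcome, and that nothing in the sizing depends on it. This stands: the flaw cannot alter the CT-FFR result, and its seriousness must be set accordingly.

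It can also be said that the event rate is unknown. Revascularization counts as MACE in patients selected for 50–70% stenosis, so events could be more frequent than in other stable disease. This too stands as a caution, but the problem persists across the whole assumed range. The 190-event arithmetic needs no rate, although ten per coefficient is only a rule of thumb. Section 4.1 can be read as 6 plus 12 months of follow-up, where section 9.2.2 says one year; the longer reading would not remove the problem.

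Three stronger readings are tempting and are not supported:

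- A reader might infer that the treatment hazard ratio cannot be estimated at any realistic event count. At least one of the 19 coefficients did diverge in about 99%, 60–65%, 33–34% and 18–20% of runs at 6, 12, 18 and 24 events. Those runs count any diverging term, usually a nuisance covariate. The group estimate itself is nearly always finite from 12 events.
- A reader might infer that the Wald test is anti-conservative throughout. At 6 events it rejected in 0% of runs with a finite estimate, because the intervals are enormous.
- A reader might infer that the same model must be run in the two subgroups, where the subgroup factor would be constant. Section 9.2.2 names no model there, so this is only a conditional concern.

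**Conclusion.** The point holds for the main MACE comparison. The prespecified model has at least 19 coefficients and no safeguard, in a trial that cannot supply ten events per coefficient even if every patient had an event. At about 6 events the treatment hazard ratio is often not finite. At 12–24 events it is finite but not trustworthy: roughly 7–11% false positives at a nominal 5%, very wide intervals at the lower counts, and estimates pushed away from 1. The inflation is moderate, and weakest at 24 events.

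These sizes rest on assumed MACE rates of 5–20%, assumed covariate prevalences and effects, and two-level coding of smoking and alcohol. The exaggeration figures are conditional on full convergence. The change should be made, but it is not a condition for a valid primary analysis.

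**What to change.** In section 9.2.2, item 3, replace the adjusted model with:

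- the number of patients with MACE and the Kaplan–Meier risk in each arm;
- a Cox model with treatment group as its only covariate, center at most as a stratum, fitted with Firth penalisation and reported with a profile-likelihood interval;
- a statement that the MACE comparison is exploratory.

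In item 4, say what is meant for MACE. If the same Cox model is intended in the diabetes and PCSK-9 inhibitor subgroups, tabulate MACE by arm there instead.

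The change should be made before unblinding. It costs wording and reduces programming. What is lost is a covariate-adjusted hazard ratio, which the data cannot support at these event counts. The group-only hazard ratio will remain imprecise, and the report should say so.

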## **4. Intervention**

### ***4.1 Drug Administration***

All eligible patients will be randomly assigned to either the experimental group or the control group. Both groups will receive conventional Western medical treatment according to the guidelines for coronary heart disease. Additionally, the experimental group will be treated with a clinically effective traditional Chinese medicine, named Qing-Xin-Jie-Yu Granules. The control group will receive a placebo treatment. The treatment period will last for 6 months, followed by a 12-month follow-up.

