#### ***4.4 Combination Drug.***

- 1) During the trial, participants are not allowed to take other traditional Chinese medicines used to treat coronary heart disease, atherosclerosis, or hyperlipidemia simultaneously.
- 2) If other medications are necessary for the treatment of other diseases, they can be continued. However, the names of the drugs (or other treatment methods), dosages, frequency of use, and timing must be documented in CRF for analysis and reporting.

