## **5.4 Endpoint**

- 1) Major adverse cardiovascular events (MACE): non-fatal myocardial infarction, cardiovascular death, and revascularization.

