## **6. Follow-up**

The treatment period will last for 6 months, and the follow-up will be a total of 12 months, with visits scheduled at the following time points: before treatment (visit 1),

2 months after treatment (visit 2), 4 months after treatment (visit 3), 6 months after treatment (visit 4), and 12 months after treatment (visit 5).

The process of discontinued case exiting the trial:

- a) Retrieve and record remaining drugs and packaging.
- b) Inquire about any adverse events or other relevant information.
- c) Perform a physical examination.
- d) Complete efficacy and safety evaluation.
- e) Record the reason for discontinuation.

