## **12. Study Flow Chart**

|                                        | Enrollment            | Treatment            |                      |                      | Close-out             |
|----------------------------------------|-----------------------|----------------------|----------------------|----------------------|-----------------------|
|                                        | Baseline
(Visit 1) | Month 2
(Visit 2) | Month 4
(Visit 3) | Month 6
(Visit 4) | Month 12
(Visit 5) |
| ENROLLMENT                      |                       |                      |                      |                      |                       |
| Eligibility screen                     | X                     |                      |                      |                      |                       |
| Informed consent                       | X                     |                      |                      |                      |                       |
| General information                    | X                     |                      |                      |                      |                       |
| Concomitant medication                 | X                     | X                    | X                    | X                    |                       |
| Symptoms and signs                     | X                     | X                    | X                    | X                    |                       |
| Allocation                             | X                     |                      |                      |                      |                       |
| INTERVENTIONS                   |                       |                      |                      |                      |                       |
| QXJYG + GDT                            | X                     | X                    | X                    | X                    |                       |
| Placebo + GDT                          | X                     | X                    | X                    | X                    |                       |
| ASSESSMENTS                     |                       |                      |                      |                      |                       |
| Efficacy outcomes        |                       |                      |                      |                      |                       |

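### The 12-month MACE hazard ratio validly estimates assignment to a six-month course, but it does not isolate the on-treatment effect, may count scan-prompted revascularisations, and runs past the last concomitant-medication record

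*Protocol*

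**What the plan says.** **Analysis.** Protocol 9.2.2, item 3, fits one Cox model with randomised group as the main independent variable. Its time axis is "the time from baseline to either the occurrence of MACE or the end of follow-up", and it yields one hazard ratio. The descriptive part reads: "The incidence rate of MACE from baseline to the 1-year follow-up will be described".

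**Treatment and follow-up.** Section 4.1 states "The treatment period will last for 6 months, followed by a 12-month follow-up". Section 6 states that "the follow-up will be a total of 12 months", and the last visit in the section 12 flow chart is Month 12.

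**Definition.** Section 5.4 defines MACE as "non-fatal myocardial infarction, cardiovascular death, and revascularization", with no qualifier on the last component.

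**Scans.** The flow chart schedules CCTA and CT-FFR for all patients at baseline and Month 6. CT-FFR is the primary efficacy outcome.

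**Other drugs.** Section 4.4 states: "During the trial, participants are not allowed to take other traditional Chinese medicines used to treat coronary heart disease, atherosclerosis, or hyperlipidemia simultaneously". It also requires other necessary medication to be documented in the CRF and names no date at which this ends. The flow chart row "Concomitant medication" is ticked at Visits 1 to 4 and left blank at Visit 5, where MACE is still collected.

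**The concern.** Drug stops part-way through the MACE window, so a single ratio combines time on drug with time off drug. A reader of the result may take it for the effect of taking QXJYG, which it need not be.

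The end of treatment is also the moment when every patient is scanned. Patients are selected for a 50% to 70% stenosis, and the blinding provisions conceal treatment group, not scan results. A procedure decided on a protocol scan alone would count as an event. If such procedures are unrelated to the drug, they pull the ratio toward 1. If they follow CT-FFR, MACE partly restates the primary outcome and is no longer separate support for it.

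Finally, 9.2.2 uses PCSK-9 inhibitor use as a MACE covariate and plans a subgroup analysis of endpoint events on it because of its expected influence. Yet the schedule collects no concomitant medication in the last part of the window. An SAP can add analyses, but it cannot recover data that the schedule never collected.

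**Working it through.** **Nothing to reproduce.** The protocol gives no MACE rate, target hazard ratio, event number or power. Its only sample size is for CT-FFR; the total of 120 (60 per arm) is used below only as the number at risk. All MACE inputs are assumptions.

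**1. Averaging over on-drug and off-drug time.** Assume few events, a constant control hazard and similar numbers at risk throughout. With f the share of the window spent on drug:

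HR(window) ≈ f × HR(on) + (1 − f) × HR(off)

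With no carry-over, HR(off) = 1. For HR(on) = 0.70:

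- 12 months in total (sections 6, 9.2.2, 12): f = 6/12, so 0.5 × 0.70 + 0.5 × 1 = 0.85.
- 6 months followed by 12 (section 4.1 read literally): f = 6/18, so 0.233 + 0.667 = 0.90.
- Effect fully persists, HR(off) = 0.70: the result is 0.70 for either length.

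Range with no carry-over:

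| HR(on) | 6+6 months | 6+12 months |
|---|---|---|
| 0.5 | 0.75 | 0.83 |
| 0.6 | 0.80 | 0.87 |
| 0.7 | 0.85 | 0.90 |
| 0.8 | 0.90 | 0.93 |

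**2. Scan-prompted procedures.** Let q be the share of control-arm events that are such procedures, equally frequent in both arms, with the remaining events split evenly over 6+6 months and no carry-over:

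HR ≈ (1 − q)/2 × HR(on) + (1 − q)/2 + q

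For HR(on) = 0.6, q = 0 gives 0.80. Assumed values of q = 10%, 25% and 50% give 0.82, 0.85 and 0.90. If instead the procedures follow CT-FFR and the drug changes CT-FFR, they differ between arms and this formula does not apply; the ratio may then move away from 1. The documents give no value for q, and q may be zero.

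**3. Precision.** Expected events = 60 × rate × (1 + HR). Power by Schoenfeld's formula for 1:1 allocation is Φ(√events × |ln HR| / 2 − 1.96). For a 12-month HR of 0.6:

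| Assumed control rate | Events | Power |
|---|---|---|
| 3% | 2.9 | 6% |
| 5% | 4.8 | 8% |
| 10% | 9.6 | 12% |
| 15% | 14.4 | 16% |

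For 80% power, 121 events would be needed. With constant hazard, a baseline-to-Month-6 ratio would rest on about half of the events shown, while the Cox model in 9.2.2 lists 17 covariates besides group.

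**4. Passages side by side.**

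- *Length of follow-up.* Section 4.1 literally gives 18 months. Section 6 gives 12 in total. Its visit times are described as being after treatment, yet the visits at 2 and 4 months fall within the treatment period, so they must count from the start of treatment. Sections 9.2.2 and 12 agree with section 6.
- *Medication.* MACE is ticked at Visits 2 to 5 and concomitant medication at Visits 1 to 4, so the period after Month 6 has no scheduled record.

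**The case against.** Three stronger conclusions are tempting, and the case against each is good.

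*That the ratio does not estimate the effect of QXJYG on MACE.* The comparison is by randomised group from baseline, so it estimates the effect of assignment to a six-month course. That is a standard treatment-policy effect, and the protocol never claims an on-drug ratio. This objection stands.

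*That the design necessarily breaks proportional hazards and dilutes the effect.* Both require the effect to end with the drug, which no section says. Several outcomes are structural (stenosis, calcification, carotid plaque), so a lasting or delayed effect is equally compatible with the text. Making a six-month ratio the main estimate would rest it on very few events and could miss a delayed benefit. This stands too.

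*That the Month-6 scan triggers events.* No section says that results reach treating physicians or lead to procedures. With blinding, any such decision is made without knowledge of arm, and procedures that follow a drug-induced change in CT-FFR are a downstream effect of the drug. This reduces the point to a risk but does not remove it: the definition admits these procedures, and nothing in the protocol identifies them.

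On medication, the ban in 4.4 can be read as covering use together with study drug, in which case ending the record at Month 6 fits the ban. The documentation duty, however, has no stated end. A drug started after Month 6 is a post-randomisation event, and adjusting for it could itself introduce bias; that is a reason to collect it for description only.

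Period-specific analyses, checks of proportional hazards and adjudication rules may be in an SAP that is not shown, so their absence is not held against the protocol.

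**Conclusion.** The concern holds in limited form. The 12-month hazard ratio is valid for assignment to a six-month course, but it does not isolate the on-treatment effect, and the protocol does not say which effect is meant. Unqualified revascularisation beside a scheduled Month-6 scan leaves room for scan-prompted events, which would either dilute MACE or tie it to CT-FFR; whether any occur cannot be told from the documents. The medication schedule does not cover the whole MACE window, and the follow-up length is contradictory.

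The size is unknown. The movement from 0.70 to 0.85 (0.90 on the literal reading of 4.1) is an illustration that rests on constant hazard and no carry-over; there is no dilution if the effect persists. MACE is neither the primary outcome nor the basis of the sample size, and events will probably be few, so these are inexpensive improvements to interpretability and do not threaten the trial's main conclusion.

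**What to change.** 1. **Reason for revascularisation.** Add a CRF field that records whether each procedure was clinically driven or prompted solely by a protocol scan, at baseline or Month 6. Tabulate it by arm, and report MACE counting only clinically driven procedures beside the figure with all revascularisations. Cost: one field and one extra summary; the restricted version has fewer events and a wider interval.
2. **Concomitant medication at Visit 5.** Tick the row at this existing visit, for description and for checking section 4.4 over the whole MACE window. Do not use it as a post-randomisation adjustment in the Cox model. Cost: one more entry at a visit already planned.
3. **Label the estimate.** Keep the 12-month hazard ratio as the main MACE result, state in 9.2.2 that it is the effect of assignment to a six-month course, and give event counts by arm for months 0–6 and 6–12 as description only. Cost: wording and one small table.
4. **Reconcile the follow-up length** across sections 4.1, 6, 9.2.2 and 12, so that the MACE window has a single meaning. Cost: wording only.

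Items 1 and 2 need to be in place while data are being collected, because neither can be rebuilt reliably afterwards.

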### **3.1 Multicenter**

This study is simultaneously conducted at 3 centers: Xiyuan Hospital of China Academy of Chinese Medical Sciences; Guan'anmen Hospital of China Academy of Chinese Medical Sciences; Beijing Tongren Hospital Affiliated to Capital Medical University.

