#### 9.2.2 Efficacy Analysis

- 1) Primary Efficacy Outcome: CT-FFR.
  - Description: CT-FFR values of the target vessels at baseline and 6 months after

treatment, as well as the difference from baseline to 6-month will be described. For multiple vessel lesions, the CT-FFR value of the most severely narrowed vessel will be selected.

- Intergroup Comparison: A linear mixed model will be used for comparison between groups. The dependent variable is the difference in CT-FFR from baseline to 6-month. Fixed effects include group and center, while random effects include subjects. Covariates include baseline values of CT-FFR, age, gender, BMI, systolic blood pressure, diastolic blood pressure, LDL-C, FBG, smoking status, alcohol consumption, family history of early-onset cardiovascular disease, presence of cerebrovascular disease, peripheral vascular disease, diabetes mellitus, hypertension, dyslipidemia, and concomitant use of PCSK-9 inhibitors.
  - Estimation: The least squares method will be used to estimate mean differences and 95% confidence intervals (CI).
- 2) Secondary Efficacy Outcomes
- a) Coronary imaging assessment indicators
- Description: %DS measurement will use the most narrowed location as the result; CACS and Gensini scores will use the total score as the result. Values of %DS, CACS, and Gensini scores at baseline and 6 months after treatment, as well as the difference from baseline to 6-month will be described.
  - Intergroup Comparison. A linear mixed model will be used, with the dependent variable being the difference from baseline to 6-month. Fixed effects include group and center, random effects include subjects, and covariates include baseline values.
  - Estimation: The least squares method will be used to estimate the mean difference and 95% CI.
- b) SAQ score
- Description: SAQ scores at baseline, 2, 4, and 6 months after treatment will be described, along with the differences from baseline to 2, 4, and 6 months.
  - Intergroup Comparisons: A mixed model for repeated measures will be used, with the dependent variable being the difference in SAQ scores at 2, 4, and 6 months relative to baseline, with the primary assessment time point at 6 months after treatment. Fixed effects include group and center, random effects include subjects. Covariates include baseline SAQ scores, visit times, the interactions between baseline and visit, and the interactions between treatment group and visit.

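### The subgroup plan is motivated by effect modification but names only patients with diabetes and PCSK-9 users, with no comparison group and no interaction, so it cannot show whether the effect differs.

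*Protocol*

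**What the plan says.** Item 4 of Protocol section 9.2.2 opens with the reason for the subgroups: "Considering the significant impact of concomitant diabetes and the use of PCSK-9 inhibitors on drug efficacy". That is a statement about effect modification. The analysis that follows is: "subgroup analysis of the primary efficacy outcome and endpoint events will be performed in SCAD patients with diabetes". The second subgroup is "SCAD patients with the use of PCSK-9". Patients without diabetes and patients not using PCSK-9 inhibitors are not mentioned, and no model is named for either subgroup.

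In the models that are specified, the two factors appear only as main effects. For CT-FFR, "Fixed effects include group and center, while random effects include subjects", and the covariate list ends with "diabetes mellitus, hypertension, dyslipidemia, and concomitant use of PCSK-9 inhibitors". The Cox model for MACE adjusts for a similar list that ends with "dyslipidemia, concomitant use of PCSK-9 inhibitors, and study center". The only interaction with treatment anywhere in the protocol is treatment group by visit, in the SAQ model.

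**The concern.** Whether diabetes or PCSK-9 inhibitor use changes the effect of the granules is a question about a difference between two effects. It needs an estimate in both levels of the factor and a direct comparison of them. The protocol plans an estimate in one level. A significant result there does not show that the factor matters, because the effect may be the same in everyone else. A non-significant result does not show loss of effect, because the subgroup is a fraction of the trial.

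What is at stake is the interpretation of a supporting analysis: a report could describe the effect as present or absent in diabetes when the data do not address that contrast. There is also a practical question of whether the subgroup models can be fitted if the long covariate lists of the main analyses are carried over.

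**Working it through.** **Inputs from the protocol.** Section 3.4 gives 120 patients, 10% dropout (120 × 0.9 = 108 evaluable), SD 0.13, a planned difference of 0.92 − 0.77 = 0.15 and a margin of 0.03 (0.15 − 0.03 = 0.12). Allocation is 1:1 (section 3.2). For centres: "This study is simultaneously conducted at 3 centers".

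**Assumptions.** The protocol gives no prevalence of diabetes or PCSK-9 use and no MACE rate. I use 20–40% diabetes (30% central), 5–10% PCSK-9 use and 2–10% one-year MACE. The value 0.075 below is half the planned difference and is also an assumption.

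**The plan's own figure.** No size or power is stated for the subgroups, so there is no subgroup figure to reproduce. The section 3.4 formula gives 2 × [(1.96 + 1.64) × 0.13 / 0.12]² + 1.96²/4 = 31.4 per group, not the stated 55. That is a separate matter; 120 is taken as stated here.

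**Step 1: power within the diabetes subgroup.** 0.30 × 108 = 32.4, about 16 per arm. SE = 0.13 × √(2/16) = 0.046; 95% half-width 1.96 × 0.046 = 0.09. Two-sided unadjusted t-test at 0.05, for an effect that is the same in all patients:

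| True effect | Power, diabetes (16 per arm) | Chance of non-significance there | Power, all (54 per arm) |
|---|---|---|---|
| 0.15 | 88% | 12% | over 99% |
| 0.12 | 72% | 28% | over 99% |
| 0.075 | 35% | 65% | 84% |

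**Step 2: parameters, if the main covariate lists were reused.** Item 4 does not say that they are. The CT-FFR model has an intercept, 1 group term, 2 centre terms and 17 covariates, 21 in all if each covariate takes one coefficient. In a subgroup the defining factor is constant and drops out, leaving 20.

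- Diabetes at 20–40% of 108: 22–43 patients. Residual degrees of freedom: 21.6 − 20 ≈ 2 to 43.2 − 20 ≈ 23. The model can be fitted but is imprecise, and very weak at the lower end.
- PCSK-9 use at 5–10% of 108: 5–11 patients for 20 parameters. The model cannot be fitted.

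**Step 3: MACE.** The Cox model has 16 covariates, 2 centre terms and group, 19 coefficients, or 18 in a subgroup. Expected events among 120 randomised:

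- Diabetes: 24 × 0.02 = 0.5 to 48 × 0.10 = 4.8.
- PCSK-9 users: 6 × 0.02 = 0.1 to 12 × 0.10 = 1.2.

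**Step 4: precision of the interaction.** SE = 0.13 × √[4/(108p) + 4/(108(1 − p))], where p is the prevalence.

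| p | SE | 95% half-width | Detectable with 80% power |
|---|---|---|---|
| 5% | 0.115 | 0.23 | 0.32 |
| 10% | 0.083 | 0.16 | 0.23 |
| 20% | 0.063 | 0.12 | 0.18 |
| 30% | 0.055 | 0.11 | 0.15 |
| 40% | 0.051 | 0.10 | 0.14 |

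**The case against.** **This is detail for the statistical analysis plan.** Much of it is. Section 3.5.3 refers to an analysis plan finalised before database lock, and a missing interaction test, reduced covariate set, minimum subgroup size or exploratory label would not be findings alone. What stands is that the protocol itself fixes the populations to be analysed, and they are one level of each factor, against its own stated reason. An analysis plan that followed the text would carry this over.

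**The text does not exclude the other patients.** True: naming a subgroup by its factor can be shorthand for splitting on it, and describing the effect within diabetes is a legitimate aim. The overall estimate is also planned, so a reader could roughly infer the effect in the rest. But no such comparison, and no interval for the difference, is specified.

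**A uniform effect would often look absent in diabetes.** A reader might infer this from the 35% power at 0.075. The planning figures do not support it: at 0.15 the effect would be missed about 12% of the time. The risk becomes large only if the true effect is well below plan.

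**The subgroup models will fail.** A reader might infer this too. It depends on reuse of the full covariate lists, which item 4 does not state, and on prevalences and event rates that the protocol does not give. For CT-FFR in diabetes the model is probably estimable.

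**An interaction test would usually be inconclusive as well.** Correct. At 30% prevalence it has 80% power only for an interaction of about 0.15, as large as the whole planned effect. The gain is an interval that addresses the right question and shows its own imprecision.

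**Conclusion.** The point holds as a mismatch between reason and method. The protocol gives effect modification by diabetes and PCSK-9 inhibitor use as the reason for the subgroups, but specifies estimation only in patients who have the factor, and carries both factors elsewhere as main effects only. The result cannot show whether the effect differs by either factor. This conclusion rests on the text alone and needs no assumed prevalence.

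The numerical consequences are conditional. Misreading a non-significant diabetes result is a modest risk at the planned effect and a serious one at half of it. Under reuse of the main covariate lists, CT-FFR could not be modelled in PCSK-9 users at 5–10% use, and subgroup Cox models would probably have too few events.

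The matter should be corrected but is limited in weight: these are supporting analyses, no stated decision depends on them, and the primary comparison is unaffected.

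**What to change.** Replace item 4 of section 9.2.2 as follows.

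- **CT-FFR and diabetes:** add a treatment-by-diabetes interaction to the CT-FFR model on the whole analysis set. Report the treatment effect with 95% CI in patients with and without diabetes, and the interaction with its 95% CI.
- **CT-FFR and PCSK-9 inhibitors:** do the same, with use defined at baseline, where each arm has enough users; otherwise tabulate. The baseline definition matters because item 4 does not date the use, and the flow chart in section 12 records concomitant medication up to month 6, so the subgroup could otherwise depend on events after randomisation.
- **MACE:** report event counts per arm in both levels of each factor instead of subgroup Cox models.
- **Status:** label all of it exploratory.

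The cost is a change of wording and one model term per factor, with no new data collection. The downside is low precision: an interaction half-width of about 0.11 at 30% prevalence, and about 0.16–0.23 at 10–5%. Failure to detect an interaction must not be reported as evidence of equal effects.
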